### Dropouts and missing data

Reasons for dropouts will be documented and reported. If patients are alive and missing at random, we will use multiple imputation methods based on ten imputed datasets with multiple imputation by chained equations [37].

### Quality control

In collaboration with community health care providers before the trial entry, health care providers in each community are responsible for monitoring patient recruitment, consent, and collection of measurements. All researchers will be trained uniformly. To prevent bias, the data will be collected with unified measurements and analytical instruments by designated personnel (not the researcher himself) who are not clearly conducting the grouping. As soon as a questionnaire is completed, it will be strictly screened, and if there is any missing data, it will be completed in time. All data collection will be completed, encoded, and inputted by two people, and questionnaires with obvious errors will be removed. Epidata3.1 will be used to establish the database, randomly check and review it at a rate of 10%, and detect errors and correct them in a timely manner.

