**Methods:**

This study is a randomized controlled trial (RCT). One of the municipal districts in Huzhou, China, will be randomly selected, and two communities with similar conditions within this district will be screened and selected. A total of 120 hypertensive patients aged 18 years and older will be recruited from these two community settings. One of the communities will be randomly allocated to an interactive pictorial health education program conducted by a comprehensive health literacy strategy that includes (i) training participants in effective health communication skills that address issues encountered in seeking medical care and (ii) the use of self-developed interactive pictorial hypertension education to improve patient understanding and behaviors versus a control group (routine community lecture health education only). The primary outcome measure is HBP-HL. Secondary outcomes are self-efficacy, self-management ability, HRQOL, social support, and improvement in blood pressure. Outcomes will be collected at 6, 9, and 12 months from trial entry.

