#### Allocation concealment

Participants and the trial coordinator will not be blinded to their group allocation; however, the data collectors and the data analyst will be blinded. The codes will be broken following statistical analysis.

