#### Outcome evaluation scales

##### Chinese high blood pressure-health literacy scale (C-HBP-HLS) [30]

This scale is divided into 5 dimensions (Print Health Literacy, Medication Label, Understanding Ability, Newest Vital Sign Test, and Avoiding Food Allergy) consisting of 15 items, which was translated into Chinese and validated by Zhang Q et al. in 2016. According to the test of functional health literacy in adults (TOFHLA) scoring system, the final total score range is 0–60 points, and the higher the score is, the higher the HL level is. Furthermore, according to the TOFHLA classification criteria, the final score of the HBP-HL scale is divided into 3 grades: a total score < 32 points reflects a lack of HBP-HL; a total score ranging from 32 to 40 points indicates an intermediate level of HBP-HL; and a total score ≥ 40 points represents a high level of HBP-HL. The Cronbach’s *α* coefficient of the scale was 0.78, and the retest reliability was 0.96.

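### Removing whole questionnaires with obvious errors can bias the health-literacy comparison; query them and set only unresolved items to missing

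*Protocol article*

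**What the plan says.** The Quality control section of the protocol article treats three kinds of data problem in three ways.

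- **Missing items.** Each questionnaire is screened as soon as it is completed, and "if there is any missing data, it will be completed in time".
- **Erroneous forms.** After a clause on completion, coding and entry by two people, the section says that "questionnaires with obvious errors will be removed".
- **Database errors.** Once the database is set up, staff are to "randomly check and review it at a rate of 10%, and detect errors and correct them in a timely manner".

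Under Dropouts and missing data, the commitment is conditional: "If patients are alive and missing at random, we will use multiple imputation methods based on ten imputed datasets". Reasons are to be documented for dropouts; removed questionnaires are not mentioned.

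The abstract states: "The primary outcome measure is HBP-HL". The scale that measures it, the C-HBP-HLS, has 15 items in five dimensions: "Print Health Literacy, Medication Label, Understanding Ability, Newest Vital Sign Test, and Avoiding Food Allergy". Eligibility requires a score below 40 on this scale, whose range is 0 to 60. Under Allocation concealment, "the data collectors and the data analyst will be blinded".

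**The concern.** The rule discards outcome data after collection. In many trials a few spoiled forms would be a nuisance and little more. Here the people completing the forms are enrolled because their health literacy is low, the primary outcome is a health-literacy score, and the intervention is meant to raise it. How well a form is filled in may track the quantity being measured. From month 6 onwards it may also track the arm, if the intervention works as hypothesised.

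A form removed because of how the participant filled it in would then be missing for a reason connected with its score. Such loss may fall outside the missing-at-random condition attached to the planned imputation, and the article does not say that removed forms enter that imputation at all. The comparison of HBP-HL between arms is at stake.

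**Working it through.** **1. What kind of error is removed.** Missing items are completed and database errors are corrected. Removal is a separate action, so the more natural reading is that it concerns how the form was filled in. The article does not say so outright.

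**2. Figures in the plan.** The removal rule carries no figure. Two figures from Sample size calculation bear on it:

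- Pilot difference: 32.09 − 27.80 = 4.29 points, with SDs of 4.89 and 4.78.
- Dropout allowance: 108 / (1 − 0.10) = 120, which reproduces the stated total and leaves 120 − 108 = 12 participants. It is described as an allowance for dropout only.

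**3. Formula.** In one arm, let *p* be the fraction of forms removed and Δ the amount by which removed forms average below those kept. The mean of all forms is the mean of kept forms − *p*Δ, so removal raises the arm mean by *p*Δ. The change in the difference (intervention minus control) is

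Δ × (*p* intervention − *p* control).

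**4. Illustration.** Assumptions, none from the document: Δ = 4.8 points (about one pilot SD), 5% removed in the intervention arm, 10% or 15% in the control arm.

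| Control removed | Change in difference | Difference seen | Share of 4.29 |
|---|---|---|---|
| 10% | 4.8 × (0.05 − 0.10) = −0.24 | 4.05 | 0.24 / 4.29 = 5.6% |
| 15% | 4.8 × (0.05 − 0.15) = −0.48 | 3.81 | 0.48 / 4.29 = 11.2% |

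If the intervention arm lost more forms instead, the same amounts would be added. With equal removal and equal Δ in both arms the change is zero.

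With 60 per arm, this scenario removes 3 intervention forms and 6 to 9 control forms, so 9 to 12 of 120 at a visit.

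**5. Can a rule applied blind give unequal loss?** This was simulated with normal scores at the pilot means and SDs. One removal rule was applied to both arms without regard to arm, with the log-odds of removal falling by 1 to 2 per SD of score. Overall removal rates and slopes are assumptions.

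| Removed overall | Difference, slope 1 to 2 | Difference, removal unrelated to score |
|---|---|---|
| 5% | 4.13 to 3.92 | 4.29 |
| 10% | 4.02 to 3.68 | 4.29 |
| 20% | 3.86 to 3.35 | 4.29 |

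At 10% overall, the intervention arm loses 6.6% to 4.8% of forms and the control arm 13.4% to 15.1%. The imbalance assumed in step 4 is therefore of a size that a score-related rule could produce. The last column shows that purely clerical removal, unrelated to score, would leave the difference unbiased.

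**The case against.** The strongest reply is that the article does not define an obvious error. Illegible, duplicate or misidentified forms fit the clause too, and need not depend on literacy. Screening each form on completion may catch many problems while the participant is present. Blinded collectors and a blinded analyst limit deliberate selection. An operational definition is also commonly left to a fuller document.

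Much of this stands. The missing definition alone is no finding. But the article does state the action, and the action is removal. The follow-up attached to screening covers missing data only, and blinding does not prevent loss that tracks literacy, as step 5 shows.

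A reader might infer more than the text supports:

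- **That data are deleted because of the outcome.** The document allows this but does not say it; clerical errors would not have that effect.
- **That wrong test answers count as errors.** Nothing says so. The C-HBP-HLS is scored from 0 to 60, with higher scores meaning higher literacy.
- **That every self-reported secondary outcome is biased.** This would need all instruments to share one form, or each to be linked to literacy. Neither is shown.
- **That removals use up the dropout allowance.** In step 4 they reach 12 only at the top of the range, and they are lost to the analysis only if they are not imputed.

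**Conclusion.** The concern holds in a limited form. The stated rule can remove primary-outcome data in a way related to the outcome and to the arm, and nothing else in the article has the removed forms queried, counted or treated as missing.

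Neither the direction nor the size of any bias can be derived from the document. If less literate control participants lose more forms, the bias is towards no effect: 0.24 to 0.48 points under the assumptions of step 4, or 6% to 11% of the pilot difference. A bias of that size would dilute an effect as large as the pilot's without hiding it. The change is still worth making, because the loss is avoidable and the remedy is cheap.

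**What to change.** Replace the removal clause in Quality control with a rule along these lines:

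- Apparent errors are queried against the participant or the source form by staff blinded to arm.
- If a query cannot be resolved, only the affected item is set to missing.
- C-HBP-HLS answers are scored as given.
- A whole form is dropped only if it is a duplicate or cannot be attributed to a participant. A total ban on removal would keep such forms and is not advised.

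In Dropouts and missing data, state that these missing values enter the planned multiple imputation. Add a sensitivity analysis that does not assume missing at random, for example one that shifts imputed C-HBP-HLS scores downwards over a stated range, separately by arm. Report the number of items set to missing and of forms dropped, by arm and visit.

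The cost is a few sentences and slightly more data-query and analysis work. The design, sample size and visit schedule do not change.

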## Discussion

This study aims to identify whether a BCW-based interactive pictorial health education program can better improve HBP-HL and HRQOL for hypertensive patients with low health literacy. The research method of heuristic questioning instead of didactic education will also demonstrate that this type of intervention can effectively mobilize the subjective initiative of hypertensive patients and provide a scientific and effective method for hypertension health management in the community. Furthermore, this study aims to provide new ideas and methods for hypertensive patients to effectively control their blood pressure and improve their HRQOL.

We hypothesize that participants in the intervention group will have effective improvements in HBP-HL, blood pressure, HRQOL, self-management ability, self-efficacy, and other patient outcomes essential in improving hypertension care when compared to the control group patients. We also hypothesize that health care providers in the intervention group will report improved health communication skills and increased knowledge and satisfaction compared to providers in the control group.

To date, very few studies combining BCW theory with interactive health education with “picture dialogue” have been designed for hypertensive Chinese patients. In light of the status quo that the prevalence of hypertension in Zhejiang Province is high but health literacy related to chronic diseases is low, if the study hypotheses are verified, a BCW-based interactive pictorial health education program could be more widely spread and applied in hypertension health care, limiting medical costs due to hypertension complications.

The key benefit of this study will be the development and application of BCW-based interactive pictorial intervention materials to promote HBP-HL in hypertensive patients with low health literacy in Huzhou. The materials developed for the project will complement and expand upon existing health education materials, such as those available from community service centers, which will focus on how to help people with low health literacy improve their health literacy levels and change unhealthy health behaviors rather than just providing information. If this project is proven effective, health care professionals and providers in community health care centers will be provided with a validated theory-based interactive pictorial health education program and will be prompted to increase its application in hypertensive patients with low health literacy.

### Dissemination policy

We will present our findings in peer-reviewed journal articles. Attendees will be informed of consent for publication to ensure their identities will not be disclosed. All methods will be carried out in accordance with SPIRIT guidelines and regulations.

### Protocol amendments

If there are any issues that may affect the trial progress and participants’ interests or safety, the protocol needs to be formally modified. These amendments need to be agreed by the Supervising Committee and approved by the Ethics Committee prior to implementation.

### Ancillary and post-trial care

Not applicable.

## Trial status

This study is ongoing. Recruitment began in July 2021 and will finish in May 2022.

## Data Availability

This is a study protocol; therefore, data sharing is not applicable, as no data are generated or analyzed.

## Abbreviations

HRQOL: Health-related quality of life
RCT: Randomized controlled trial
AHA: American Heart Association
BCW: Behavior change wheel
HBP-HL: High blood pressure health literacy
C-HBP-HLS: Chinese High Blood Pressure-Health Literacy Scale
HPSMBRS: Hypertensive Patients’ Self-Management Behavior Rating Scale
CDSMP: Chronic Disease Self-Management Program
